#### Randomization and blinding procedure

a list of random numbers will be created, using statistical software, to which the researchers involved in the study will not have access. This list will be applied to the list of participating Clinics until the clusters for each group are obtained. Three types of cluster will be used, according to the treatment for the venous leg ulcer provided at the Clinic (**A: **compression therapy plus simple, low-adherence dressings and acupuncture; **B: **compression therapy plus special dressings; **C: **compression therapy plus simple, low-adherence dressings). Before beginning, the list of Clinics will be randomly ordered, by drawing lots blindly, with no repetitions, from a bag containing the names of all the Clinics taking part. None of those participating in this process will belong to the research group, and none of them will play any further part in the study.

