### Sample size

The sample size has been calculated following the parameters of Campbell et al. [41], on the basis of historical data [18]. The success rate for complete healing of venous leg ulcers at 3 months, with compression bandaging plus special dressings, is 44%. With an alpha (significance) level of 0.05 and a power of detection of differences of 80%, assuming a two-tailed approach, the total sample size needed will be 375 patients, in order to detect differences of 15% between the groups, as regards the rate of complete healing of venous leg ulcers at 3 months. This calculation assumes a possible dropout rate of 5% and an intra-cluster coefficient of correlation of 0.05 (according to the expected variance of the response within a single cluster). There will be 15 clusters (Primary Healthcare Clinics) and so each Clinic will need to recruit 25 subjects. Therefore, 3 treatment arms will be formed, with 125 patients in each (with 5 Clinics per arm).

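### The clinic draw is valid but unstratified; blocking 15 clinics in threes and pre-specifying one clinic covariate would cheaply reduce a chance arm difference whose SD is about 7 points

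*Protocol article*

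**What the plan says.** Randomization and blinding procedure describes one draw over all clinics. First, "the list of Clinics will be randomly ordered, by drawing lots blindly, with no repetitions", from a single container holding every clinic's name. A random-number list is then used: "This list will be applied to the list of participating Clinics until the clusters for each group are obtained". No strata, blocks, matching or balance constraint on clinic characteristics is named.

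Sample size fixes the scale: "There will be 15 clusters (Primary Healthcare Clinics) and so each Clinic will need to recruit 25 subjects", with five clinics in each of three arms. The aim is "to detect differences of 15% between the groups" in 3-month healing, from a reference rate of 44%, with "an intra-cluster coefficient of correlation of 0.05" and 5% dropout.

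Data analysis plans baseline comparisons at cluster or individual level. It then plans a multilevel model, with patients at level 1 and clinics at level 2, to adjust for variables that turn out unbalanced. The Discussion lists variability in nursing care as a limitation and answers it with standardisation and analysis after the event.

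**The concern.** With five clinics per arm, the mix of clinics an arm happens to receive enters every treatment contrast. Clinics may differ in case mix and in nursing practice, and the ICC in the sample size section concedes that their healing rates differ. A draw that ignores any known clinic characteristic leaves all of that variation to chance. The remedy left in the plan is to adjust for variables found unbalanced afterwards. That selection depends on the data and has only 15 clinics to support it. At stake is precision, and how convincing the result looks if the arms turn out visibly different at clinic level.

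**Working it through.** **Inputs from Sample size:** ICC 0.05; healing 44%; target 15 points; 15 clinics, 5 per arm, 25 patients each; dropout 5%, so 25 × 0.95 = 23.75 evaluable per clinic. **Assumed, not in the documents:** the share f of between-clinic variance that a ranking variable explains.

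The plan gives no figure for chance imbalance, so there is none to reproduce.

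**1. Size of the chance difference.**
- Between-clinic SD = √(0.05 × 0.44 × 0.56) = √0.01232 = 0.111, or 11.1 points.
- SD of the difference between two means of five clinics = 0.111 × √(2/5) = 0.070, or 7.0 points, about 47% of the 15-point target.

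The table gives normal tail probabilities for a given pair and simulated values for the largest of the three gaps.

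| Gap above | Given pair | At least one of three pairs |
|---|---|---|
| 7.5 points | 28% | 53% |
| 10 points | 15% | 33% |
| 15 points | 3% | 8% |

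The result depends on the ICC. The 33% becomes 0.4% at ICC 0.01, 6% at 0.02 and 57% at 0.10.

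**2. Effect of blocking the draw.** The simulation used a normally distributed ranking variable, 15 clinics sorted into five blocks of three, and A, B and C drawn once per block. It keeps the spread that remains within a block. The chance that at least one pair differs by more than 10 points is:
- f = 0: 33%
- f = 0.20: 26%
- f = 0.40: 18%
- f = 0.60: 10%

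Treating clinics within a block as identical on the ranking variable would give 25%, 16% and 6%, which is too favourable.

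**3. Effect of modelling the variable.** Variance of a clinic mean = 0.01232 between clinics + 0.95 × 0.2464 / 23.75 = 0.00986 within clinics, in total 0.02218. The between-clinic share is 0.01232 / 0.02218 = 0.556. A covariate explaining f of it cuts the variance of a contrast by 0.556 × f: 0%, 11%, 22% and 33% for f = 0, 0.20, 0.40 and 0.60.

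**4. Cost in degrees of freedom.** A three-arm analysis of 15 clinic means has 15 − 3 = 12 df; one clinic-level covariate leaves 11. Power for 44% against 59% (noncentral t, 25 per clinic) is 31.9% without the covariate. With it, power is 31.5% at f = 0, 32.3% at 0.05, 34.8% at 0.20, 39.0% at 0.40 and about 44.4% at 0.60. The worst case loses 31.9 − 31.5 = 0.4 points, and break-even lies below f = 0.05.

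**5. What this cannot repair.** A simple comparison of 44% with 59% needs 174 patients per arm. With m patients per clinic, the number of clinics per arm is 174 × [1 + (m − 1) × 0.05] / m. As m grows this tends to 174 × 0.05 = 8.7, so at least nine clinics per arm are needed however many patients each recruits.

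**The case against.** Randomising 15 clinics 5:5:5 is sound. Clinic variation adds variance, not bias, and it is the very quantity the ICC represents. That stands, and it is why this is an improvement rather than an error. A reader might infer from the small number of clinics that the comparison is biased, or that large imbalance is likely. The documents support neither: a gap above 10 points has a 15% chance for a given pair, and a gap as large as the target has 3%. The 10-point mark is itself a reviewer's choice.

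The benefit is also unproven. The documents name no clinic-level predictor of healing and report no clinic healing rates. Even the previous year's rate is limited by its reliability, n × 0.05 / [1 + (n − 1) × 0.05]. This is 0.57 with 25 patients per clinic and 0.44 with 15 (counts assumed, clinic effects assumed stable), so f = 0.60 is out of reach at such counts. List size or caseload might explain almost nothing. This stands too.

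Blocking can cost power. With a term for every block (12 to 8 df), blocks must explain about 15% of between-clinic variance to pay back; if only two arms are analysed (8 to 4 df), about 42%. That applies to block terms and not to a single covariate.

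The planned multilevel model gives some protection, and patient-level covariates may absorb differences in case mix. But the adjustment set is chosen after imbalance is seen.

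Finally, the study period starts in April 2008 and the article appeared in June 2008, so the draw may already have been made. In that case only the covariate remains open.

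**Conclusion.** The point holds as a cheap improvement. The allocation is valid but uses no information about the clinics. On the plan's own inputs, clinic mix alone gives a chance difference between two arms with an SD of about 7 points against a 15-point target, and a 33% chance that some pair differs by more than 10 points. Blocking would bring this to between 33% and 10%, depending on how well the ranking variable predicts healing, for which the documents give no figure. The calculation rests on ICC 0.05, equal clinic sizes, approximately normal clinic effects and the 3-month healing scale used for the sample size; the primary outcome is time to healing. A reader might also infer that blocking would rescue the trial's power. It would not: with the single covariate and f = 0.60, power is still about 44%.

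**What to change.** Before the draw:

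1. Choose one clinic-level variable expected to predict healing, for example the previous year's healing rate or the venous-ulcer caseload.
2. Rank the 15 clinics on it and form five blocks of three.
3. Have the same independent persons draw A, B and C once within each block.
4. Pre-specify that variable as a single clinic-level covariate in the primary model, without a term per block.

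If the draw has been made, keep it and pre-specify only the covariate, before outcomes are examined.

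The cost is one figure per clinic, a modified draw, one between-clinic degree of freedom (about 0.4 points of power if the variable is uninformative) and slightly more predictable allocation within a block. No extra patients are needed. The number of clinics per arm has to be addressed separately.

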### Ethical criteria

The ethical validity of this study has been analyzed and approved by the Andalusian Government Committee for Clinical Trials, following the approval of the corresponding Research Commission at each of the participating Clinics. The study design takes into account the fundamental principles set out in the Helsinki Declaration, and those of the Council of Europe Convention concerning human rights and biomedicine, as well as the requirements under Spanish law in the field of biomedical research, the protection of personal data, and bioethics. All the patients involved must sign their informed consent to the proposed clinical research procedures. During the course of the study, audits will be performed as required by the relevant Research and Ethics Committee, as well as those of each Clinic's Quality Committee, independently of any external audits (such as that of the research financing body) that may be necessary.

### Sample size

The sample size has been calculated following the parameters of Campbell et al. [41], on the basis of historical data [18]. The success rate for complete healing of venous leg ulcers at 3 months, with compression bandaging plus special dressings, is 44%. With an alpha (significance) level of 0.05 and a power of detection of differences of 80%, assuming a two-tailed approach, the total sample size needed will be 375 patients, in order to detect differences of 15% between the groups, as regards the rate of complete healing of venous leg ulcers at 3 months. This calculation assumes a possible dropout rate of 5% and an intra-cluster coefficient of correlation of 0.05 (according to the expected variance of the response within a single cluster). There will be 15 clusters (Primary Healthcare Clinics) and so each Clinic will need to recruit 25 subjects. Therefore, 3 treatment arms will be formed, with 125 patients in each (with 5 Clinics per arm).

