### Outcome measures

#### Primary outcome

##### Time until complete healing is achieved

Complete healing is defined as the complete epithelialization of all the leg venous ulcers, not just the reference one.

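### On the plan's own inputs, 125 patients in 5 clinics per arm give about 29–39% power for a 15-point difference in 3-month healing, not 80%

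*Protocol article*

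**What the plan says.** The Sample size section of the protocol article gives every input needed to check its result:

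- Reference rate: "The success rate for complete healing of venous leg ulcers at 3 months, with compression bandaging plus special dressings, is 44"%.
- Error rates: "With an alpha (significance) level of 0.05 and a power of detection of differences of 80"%, "assuming a two-tailed approach".
- Allowances already included: "a possible dropout rate of 5% and an intra-cluster coefficient of correlation of 0.05".
- Result: "the total sample size needed will be 375 patients, in order to detect differences of 15% between the groups", on the 3-month complete-healing rate.
- Layout: 15 clinics recruiting 25 patients each, so that "3 treatment arms will be formed, with 125 patients in each (with 5 Clinics per arm".

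Under Outcome measures, the primary outcome is "Time until complete healing is achieved". Complete healing at 3 months, on which the calculation rests, is listed under Secondary outcome variables.

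**The concern.** The design effect alone is 2.2, so an arm of 125 carries the information of about 57 independent patients. That is far too few to separate 44% from 59%, or from 29%, with 80% power. If so, the only power statement in the article is wrong on its own inputs. A true 15-point difference in the 3-month rate would then be missed roughly two times in three, while a reader would believe the risk to be one in five.

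**Working it through.** **Inputs** (all from the Sample size section): p1 = 0.44; difference 0.15, direction not stated, so p2 = 0.59 or 0.29; two-sided alpha 0.05; power 0.80; ICC 0.05; 25 patients per clinic; 5 clinics per arm; 5% dropout.

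**Step 1. Required size.**

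- Unpooled formula: n = (1.960 + 0.842)² × [p1(1−p1) + p2(1−p2)] / 0.15², with (1.960 + 0.842)² = 7.849. The pooled formula uses the average proportion for the variance under the null hypothesis.
- Design effect: 1 + (25 − 1) × 0.05 = 2.2.
- Dropout: divide by 0.95.

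| Comparison | Formula | Individual n per arm | × 2.2 | ÷ 0.95 | Three arms |
|---|---|---|---|---|---|
| 44% vs 59% | unpooled | 7.849 × 0.4883 / 0.0225 = 170.3 | 374.7 | 394.5 | 1,183 |
| 44% vs 59% | pooled | 173.1 | 380.8 | 400.8 | 1,202 |
| 44% vs 29% | unpooled | 7.849 × 0.4523 / 0.0225 = 157.8 | 347.1 | 365.4 | 1,096 |
| 44% vs 29% | pooled | 160.5 | 353.1 | 371.7 | 1,115 |

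At 25 per clinic, 365–401 per arm is 14.6–16.0 clinics, so 15–16 in practice (the highest figure is fractionally over 16).

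**Step 2. Can 375 be reproduced?** Not as a three-arm total from all the stated inputs. It lies close to the per-arm figures: 374.7 (44% vs 59%, unpooled, before dropout) and 371.7 (44% vs 29%, pooled, with dropout). It is also close to 374 = 2 × 187, a two-arm total with continuity correction but no design effect and no dropout. The last breaks the stated inputs.

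**Step 3. Power as planned.** Without dropout, the effective size per arm is 125 / 2.2 = 56.8. With dropout there are 23.75 completers per clinic, the design effect is 1 + 22.75 × 0.05 = 2.1375, and the effective size is 118.75 / 2.1375 = 55.6. For 44% vs 59% the standard error at 55.6 is √(0.4883 / 55.6) = 0.0938, so the standardised difference is 0.15 / 0.0938 = 1.60. About 2.80 is needed for 80% power.

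| Reference distribution | 44% vs 59% | 44% vs 29% |
|---|---|---|
| Normal, pooled or unpooled | 35–37% | 37–39% |
| t, 12 df (15 clinics, 3 arms) | 31–32% | 33–34% |
| t, 8 df (10 clinics, 2 arms) | 29–30% | 31–32% |

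The t rows allow for having only 5 clinics per arm. A simulation with a t-test on clinic proportions gives 29–32%.

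**Step 4. What the result depends on.**

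- No clustering and no dropout: 125 per arm gives 66–70% (normal).
- ICC 0.01: 46–61% over the same tests and directions.
- Larger clinics at ICC 0.05: effective size per arm cannot exceed 5 / 0.05 = 100, below the 158–173 needed. The minimum number of clinics is n × ICC = 7.9–8.7 per arm, even with unlimited patients in each.
- Difference detectable with 80% power: 24–26 points (normal), 26–29 points (t, 8–12 df).

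**The case against.** Nothing elsewhere in the article rescues the 80%. The main defences can be taken in turn.

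- *The ICC is cautious.* Removing clustering altogether still leaves power at 70% or less.
- *375 may be a two-arm total.* The text divides it over three arms. Even 187.5 per arm gives only about 49–53%.
- *The 15% may be relative.* The requirement then rises to about 2,000 or more per arm.
- *The full protocol or analysis plan may hold the detail.* The point is not an omission: the inputs and the result are both printed and disagree.

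Other objections do limit what may be said.

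- **How 375 arose.** A reader might infer that a per-arm figure was certainly labelled as a total and divided by three. The closest match, 374.7, leaves out the dropout that the text says is included, and other routes come near 375. The explanation is likely, not established, and the shortfall does not depend on it.
- **The primary outcome.** A reader might infer that time to healing has the same low power. The article gives neither a target hazard ratio nor the proportion expected to heal by 12 months, so any figure would rest on added assumptions. None is claimed here.
- **Reading a null result.** A reader might infer that a non-significant result will be reported as no benefit. No section says so, and Data analysis plans 95% confidence intervals.
- **The reference rate.** The 44% belongs to the special-dressings arm, not the control arm. Since special dressings are a named comparator in the research questions, this is not in itself an error.

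**Conclusion.** The concern holds for the stated 3-month calculation. On the plan's own inputs the requirement is about 365–401 patients per arm (roughly 1,100–1,200 in total), against 125 per arm (375 in total). Power per pairwise comparison is about 29–39%: 35–39% by normal approximation and 29–34% with a t reference that respects the number of clinics.

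This rests on reading the 15% as an absolute difference in either direction, equal clinic sizes, and no adjustment for multiple comparisons. Adjusting over three comparisons would lower power further, to about 21–23% (Bonferroni, normal approximation). The conclusion does not hinge on the ICC, on the choice of formula, or on how 375 came about.

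**What to change.** Rewrite the Sample size paragraph to say that:

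- 375 patients in 15 clinics give about 29–39% power per pairwise comparison for a 15-point difference in 3-month healing, at ICC 0.05 with 5% dropout;
- 80% power is reached only for differences of about 24–29 points;
- 80% power for 15 points would need about 15–16 clinics of 25 patients per arm, and enlarging the existing clinics cannot achieve it;
- the calculation concerns a secondary outcome and does not cover the primary outcome, time to complete healing.

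If a smaller ICC was intended, state it and recompute; a value of 0.01 would still give only about 46–61%.

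The correction is wording only and needs no extra patients. Its cost is a much less favourable stated power. Adding clinics would be a separate decision for the sponsor.

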**Discussion:**

The results will be measured and recorded in terms of the median time elapsed until complete healing of the ulcer, and the rate of complete healing at 3 months after beginning the treatment. An economic analysis will also be made.

This study, carried out in the context of real clinical practice, will provide information for decision-taking concerning the effectiveness of special dressings. Moreover, for the first time a high-quality study will evaluate the effectiveness of acupuncture in the process of healing venous leg ulcers.

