#### Secondary outcome variables

##### Complete healing at 3 months after beginning treatment

Complete healing is defined as the complete epithelialization of all the leg venous ulcers, not just the reference one (table 1).

**Table 1 T1:** Outcome measures. Work scheme with description of assessment visits and times.

	**Baseline (T0)**	**Weekly treatment**	**Evaluation at 3 months (T1)**	**Weekly treatment (if necessary)**	**Evaluation at 6 months (T2)**	**Evaluation at 12 months (T3)**
Sociodemographic data	X					
Ankle/arm index	X					
Nutritional study	X					
Localization of ulcer(s)	X		X		X	X
Area of main ulcer	X	X	X	X	X	X
Duration of the main ulcer	X					
Exudate culture (if necessary)	X	X	X	X	X	X
Changes in the size of the main ulcer		X	X	X	X	X
Characteristics of the main ulcer	X	X	X	X	X	X
Complete healing (date)		X	X	X	X	X
Pain intensity		X	X	X	X	X
SF-12	X		X		X	X
Adverse events/effects		X	X	X	X	X
Compliance with hygiene-posture recommendations	X		X		X	X
Location of treatment (clinic/home)		X		X		
Time employed in treatment		X		X		
Materials employed in treatment		X		X		
Number of needles used(Group A)		X		X		
Obtention of Deqi (Group A)		X		X		

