### Data analysis

The data analysis will be carried out by personnel blinded to the treatment groups, and for two types of populations: (1) intention to treat (ITT), with all the patients randomized; (2) per protocol (PP), including only the patients with no more than slight variances from the protocol.

The baseline variables for the different groups will be compared, to test the homogeneity produced by random allocation, in terms of differences of the means and of proportions, and the only differences taken into consideration in this comparison will be those that are clinically relevant for subsequent analysis. The magnitude of the difference in any imbalance produced by the random allocation to groups will be evaluated by using ratios of the means, or medians, or proportions, bearing in mind whether the level of analysis is per cluster or per individual.

The final analysis will be carried out as a univariate survival analysis (using the Kaplan-Meyer method and the log-rank-test for inter-group comparison). The hazard ratios for each treatment will be calculated, together with the corresponding NNTs, calculating a 95% confidence interval, using Cox's proportional risk regression model. The assumption of proportionality will be assessed from the interaction between the time elapsed until success (total healing) and treatment group, and will be tested graphically by observing the parallelism in the log-log curves. A multilevel analysis will be carried out to adjust for possible unbalanced variables in the baseline analysis, taking the patients as level 1 and the Primary Healthcare Clinics as level 2. The interactions between clinic and treatment group will be examined, as will the possible variability in the intercept. The level of significance will be set at p < 0.05, for all the tests made. Cost-effectiveness, cost-utility and opportunity cost analyses will be made.

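### The only stated target difference and 80% power are for 3-month healing, a secondary outcome; the primary outcome, time to healing, has neither, and its cluster-adjusted power is about 58% or less for the upward difference

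*Protocol article*

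**What the plan says.** All references are to the protocol article.

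- **Outcome measures, Primary outcome** has one entry: "Time until complete healing is achieved".
- **Secondary outcome variables** opens with "Complete healing at 3 months after beginning treatment".
- **Sample size** starts from a historical 3-month healing rate of 44% with special dressings. Taking two-sided alpha 0.05 and 80% power, it arrives at a total of 375 and gives the purpose as "in order to detect differences of 15% between the groups, as regards the rate of complete healing of venous leg ulcers at 3 months". The inputs are 5% dropout, an intra-cluster correlation of 0.05, 15 clinics of 25 patients, and so 125 patients and 5 clinics per arm. It gives no hazard ratio, median time or number of healings.
- **Interventions** sets follow-up at one year.
- **Data analysis** makes the final analysis a survival analysis (Kaplan-Meier, log-rank, Cox). This fits the primary outcome and not the quantity used for sizing.

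**The concern.** The outcome that justifies the sample size is not the one that decides the trial. A reader who sees 80% under Sample size will take it as the chance that the primary analysis detects the effect of interest, but the figure was set for a different outcome.

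The two outcomes do not share a power. One uses healing status at 3 months; the other uses every healing over 12 months. How they compare depends on the healing curve after 3 months, on which the sizing section is silent. If the primary result is not significant, nobody can tell from the plan whether the trial could have detected the effect it was looking for.

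**Working it through.** **Inputs from the article.** Two-sided alpha 0.05; power 80%; 44% healed at 3 months; difference 15 points; intra-cluster correlation 0.05; 25 per clinic; 125 per arm; 5% dropout; 12 months of follow-up. The article does not give the direction of the difference; 59% is taken first, then 29%.

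**Derived.** Evaluable per arm: 125 × 0.95 = 118.75. Design effect: 1 + (25 − 1) × 0.05 = 2.2.

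**The plan's own figure.** For 44% versus 59% the usual two-proportion formula needs 174 per arm; × 2.2 = 383; ÷ 0.95 = 403; three arms make about 1,209. The stated 375 is not reproduced. With 118.75 per arm, power for the 3-month rate is about 64% ignoring clustering and about 34% with the design effect. That arithmetic is a separate fault; correcting it would still leave the primary outcome without a target or a power.

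**Target effect on the primary scale.** Under proportional hazards,
HR = ln(1 − 0.59) / ln(1 − 0.44) = 1.54, and ln HR = 0.430.

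**Healings needed (Schoenfeld).** 4 × (1.96 + 0.84)² / 0.430² = 170 per pairwise comparison before clustering; 170 × 2.2 = 374 with it. Two arms hold only 2 × 118.75 = 237.5 evaluable patients, so on this approximation 80% is out of reach even if every patient healed.

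**Power with constant hazards (assumption).**
- Healed by 12 months: 1 − 0.56⁴ = 0.902 and 1 − 0.41⁴ = 0.972.
- Healings: 118.75 × (0.902 + 0.972) = 222.5.
- Power = Φ(½ × √events × 0.430 − 1.96).
- Ignoring clustering: Φ(3.21 − 1.96) = 89%.
- With the design effect, 222.5 / 2.2 = 101.1 effective events: Φ(2.16 − 1.96) = 58%.

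**Power if healing slows after 3 months.** The Background reports 40–70% healed at 3 months and 50–80% at 6 months. Pairing the ends of those ranges (assumption), the later rate relative to the early one is ln(0.6/0.5) / −ln(0.6) = 0.36 and ln(0.3/0.2) / −ln(0.3) = 0.34. With a later rate of f times the early rate in both arms, 12-month healing is 1 − 0.56^(1+3f) and 1 − 0.41^(1+3f):

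| f (assumed) | Healed at 12 months | Healings | Power, no clustering | Power, design effect 2.2 |
|---|---|---|---|---|
| 1 | 90% / 97% | 222 | 89% | 58% |
| 0.5 | 76% / 89% | 197 | 86% | 53% |
| 0.35 | 70% / 84% | 182 | 83% | 50% |
| 0.2 | 61% / 76% | 162 | 78% | 45% |

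**Opposite direction.** For 44% versus 29%, HR = ln(0.71) / ln(0.56) = 0.59. Cluster-adjusted power at 12 months is about 70% with constant hazards and about 50 to 61% for f = 0.2 to 0.5.

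**The case against.** **The mismatch need not cost power.** Under proportional hazards the log-rank test over 12 months has more power than the 3-month comparison at the same size (58% against 34% with clustering, 89% against 64% without). Sizing on the 3-month rate would then be cautious. This stands: the low figures come from 375 patients meeting a design effect of 2.2, not from the choice of outcome. It does not rescue the stated 80%, which still describes neither comparison on the plan's own intra-cluster correlation.

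**Constant hazards are generous.** They imply 64% and 91% healed at 6 months from 40% and 70% at 3 months, above the Background's 50% and 80%. This also stands, and is why the answer is given as a range.

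**Readings that go too far.** A reader might infer from the abstract, which says results will be measured as "the median time elapsed until complete healing of the ulcer, and the rate of complete healing at 3 months after beginning the treatment", and from the rule "The level of significance will be set at p < 0.05, for all the tests made", that the two healing results have no order and either can be claimed as the trial's answer, with an inflated error rate. The text does not support this. The outcome section names one primary and puts 3-month healing among the secondaries. Data analysis names no separate test of the 3-month rate. A single primary at 0.05 needs no adjustment for a secondary, and a testing order for secondaries is commonly left to an analysis plan.

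A reader might also suppose that an acupuncture effect would show at 3 months and fade from the 12-month test. That requires an effect confined to the first 3 months, but Interventions continues sessions for up to 6 months in patients whose ulcers have not healed.

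**Conclusion.** The point holds as a fault in the stated power. The article attaches its only target difference and its 80% to a secondary outcome and gives the named primary none. For one pairwise comparison at the size planned, power for time to healing is about 58% with constant hazards and about 45 to 53% if later healing is slower; the opposite direction gives about 50 to 70%.

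These figures assume proportional hazards, the Schoenfeld approximation, no healings counted from the 5% who drop out, and the 3-month intra-cluster correlation carried over to time to healing as a design effect of 2.2. Using 23.75 evaluable patients per clinic instead gives 2.14 and about 59%, so the conclusion does not turn on that choice. Ignoring clustering lifts the figure to about 89%, but the plan randomises clinics and itself assumes correlation within them.

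Nothing here shows that the primary outcome is undefined or that the type I error is inflated.

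**What to change.** Under Sample size:

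1. State the target effect for time to complete healing. If the intended difference is 44% versus 59% at 3 months, that is a hazard ratio of about 1.54 under proportional hazards; also say which direction and which arm comparison is meant.
2. Give the cluster-adjusted power for that comparison with 15 clinics and 375 patients, and show how it varies with the assumed healing curve after 3 months.
3. Keep the 3-month calculation, once its arithmetic is checked, but label it as power for the secondary outcome.

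The cost is one calculation and a few sentences, with no extra patients and no change to treatment or follow-up. The downside is that the stated power becomes less favourable.
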